## Abstract

**Background:**

Tinnitus is the result of aberrant neuronal activity. As a novel treatment form, neuromodulation is used to modify neuronal activity of brain areas involved in tinnitus generation. Among the different forms of electric stimulation, transcranial random noise stimulation (tRNS) has been shown to be a promising treatment option for tinnitus. In addition, recent studies indicate that the reduction in tinnitus can be more pronounced when different modalities of stimulation techniques are combined (“bimodal stimulation”). TRNS can be used in combination with acoustic stimulation (AS), a further treatment option recognized in the literature. The aim of the proposed study is to investigate whether simultaneous tRNS and AS improve levels of tinnitus loudness and distress.

**Methods:**

The intervention consists of bilateral high-definition tRNS (HD-tRNS) over the auditory cortex combined with the application of AS which is studied in a crossover design. The visits will be performed in 26 sessions. There will be 20 treatment sessions, divided into two blocks: active and sham HD-tRNS. Within the blocks, the interventions are divided into group A: HD-tRNS and AS, and group B: HD-tRNS alone. Furthermore, in addition to the assessments directly following the intervention sessions, there will be six extra sessions performed subsequently at the end of each block, after a period of some days (follow-ups 1 and 2) and a month after the last intervention (C). Primary outcome measures are analog scales for evaluation of subjective tinnitus loudness and distress, and the audiological measurement of minimum masking level (MML). Secondary outcome measures are brain activity as measured by electroencephalography and standardized questionnaires for evaluating tinnitus distress and severity.

**Discussion:**

To the best of our knowledge, this is the first study which uses HD-tRNS combined with AS for tinnitus treatment. The crossover design permits the comparison between HD-tRNS active vs. sham and with vs. without AS. Thus, it will be possible to evaluate the efficacy of the combined approach to HD-tRNS alone. In addition, the use of different objective and subjective evaluations for tinnitus enable more reliable and valid results.

**Trial registration:**

Swiss Ethics Committee (BASEC-Nr. 2020-02027); Swiss Federal Complementary Database (kofam.ch: SNCTP000004051); and ClinicalTrials.gov (clinicaltrials.gov: NCT04551404).

## Administrative information

Note: the numbers in curly brackets in this protocol refer to SPIRIT checklist item numbers. The order of the items has been modified to group similar items (see https://www.equator-network.org/reporting-guidelines/spirit-2013-statement-defining-standard-protocol-items-for-clinical-trials/)

**Role of sponsor {5c}**	Investigator initiated the research.

## Introduction

### Background and rationale {6a}

Tinnitus is the result of aberrant neuronal activity within the auditory pathways. This activity is erroneously interpreted as sound by the auditory centers [1, 2]. It is present in 10–20% of the population, and the prevalence increases with advancing age, occurring in more than 30% of elderly people [3].

Many pathologies can result in tinnitus, the perception of which involves different areas of the nervous system, and finally results in abnormal cortical activity [1]. The structural and functional alterations are observed in the auditory cortex and non-auditory brain areas such as the cingulate cortex, dorsolateral prefrontal cortex, insula, hippocampus, caudate nucleus, and corona radiata, among others [4–7]. Tinnitus originates in the auditory system, but changes in functional connectivity and neuronal activity of non-auditory systems influence the perception, persistence, and severity of tinnitus [8].

As a treatment form, neuromodulation can be used to modify neuronal activity of brain areas involved in the perception of tinnitus [9]. There are different types of non-invasive and invasive brain stimulation [10]. Among the different forms of non-invasive transcranial electric stimulation (tES) [11–13], we differentiate between transcranial direct current stimulation (tDCS), which is the most established and widely used method applying constant direct current; transcranial alternating current stimulation (tACS) using sinusoidal current in a fixed frequency; and transcranial random noise stimulation (tRNS), which is a subform of tACS in which a range of low- and high-frequency alternating currents are generated randomly.

TRNS has previously been demonstrated to reliably increase the cortical excitability up to 1 h after a stimulation of 10 min [14, 15]. The method could also show reliable changes in cortical activity in the auditory cortex (T7 and T8) after tRNS stimulation [16]. The effect of tRNS on the subjective perception of tinnitus can be found in eight original studies which, given the novelty and putative efficacy of the method, were all recently published [17–24]. Thus, it is important to compare the differences, implications, and limitations between them. The method showed few differences between the studies, with more variations in the number of sessions. The treatment was performed using the intensity of 2 mA in seven studies [17–23] and 1.5 mA in one study [24]. All studies performed the stimulation for 20 min, either alone or in combination with other treatments [17–24]. The number of sessions ranged between one session [17, 20–22, 24], eight sessions in 4 weeks [23], and 10 consecutive daily sessions [18]. A case report conducted the stimulation with 2–3 days between sessions, although the total number of sessions was not mentioned in this report [19]. All studies used a pair of surface sponge electrodes with 35 cm^2^ placed in saline solution [17–24].

Some studies analyzed the effect of stimulation with electrodes over the bilateral temporal cortex (T3/T7 and T4/T8) [17–19, 24]; or used these positions (T3 and T4), and compared this montage with dorsolateral prefrontal cortex stimulation (F4 and FP1) [20–22]. Others compared alternative neuromodulatory techniques, for example, tDCS and tACS, in the same montage [24]; or bifrontal (F3 and F4) tDCS alone with multisite tDCS and tRNS (T3 and T4) [23].

The results were presented differently based on the objectives of each study. A study conducted by Joos et al. [17] compared different types of frequency bands used for tRNS. A decrease in tinnitus loudness and distress could be observed in the groups that received low-frequency stimulation (lf-tRNS; 0.1–100 Hz) and high-frequency stimulation (hf-tRNS; 100–640 Hz), but no substantial effect could be obtained for the group that received whole-frequency spectrum tRNS (wf-tRNS) [17]. However, it is important to note the large difference between the number of patients, lf-tRNS (*n* = 119), hf-tRNS (*n* = 19), and wf-tRNS (*n* = 16), and the absence of a control group to assess the effectiveness of the therapy [17].

Another study evaluated the tRNS alone and did not find significant efficacy of hf-tRNS, since only eight patients (27%) responded positively for the reduction of tinnitus loudness, tinnitus distress, unpleasantness, and depression [18]. A possible bias in the results was the use of repetitive transcranial magnetic stimulation (rTMS) treatment before tRNS and the absence of a sham group [18]. In a case study of tinnitus associated with red ear syndrome, substantial alleviation of pain intensity, and a prolongation of the interval between attacks was observed, although the tinnitus complaints did not change [19].

Three studies by the same authors with similar characteristics have been published [20–22]. The multisite protocol, in a sham-controlled clinical trial with lf-tRNS, observed a reduction in tinnitus loudness in the real condition, for both multisite and auditory cortex groups [20–22]. A reduction in tinnitus distress was only found in the multisite group. Multisite tRNS has been shown to be more effective in reducing tinnitus loudness and distress [21]. The other study used resting-state EEG analysis to assess lf-tRNS stimulations effects. In the multisite tRNS group (10 min tRNS in auditory cortex – T3 and T4 + 10 min of dorsolateral prefrontal cortex – F4 and FP1), an increase in power was identified in the alpha-1 band at the auditory and prefrontal cortex accompanied by a decrease in power in the delta and beta-2 bands in the prefrontal cortex, anterior cingulate cortex, and the parahippocampus. Furthermore, decreased alpha connectivity between the right prefrontal cortex and the left auditory cortex was observed in the same group. However, the study did not test a group with dorsolateral prefrontal cortex (DLPFC) stimulation alone [20]. In the comparison between two different groups receiving multisite tRNS, comparing 1 session (*n* = 17) vs. eight sessions over 4 weeks (*n* = 12), a reduction in tinnitus loudness and distress occurred in both groups, but with a higher suppression in the multiple-session group [22].

To et al. [23] compared different types of TES in three groups: one group received bifrontal tDCS, the second group received multisite treatment of bifrontal tDCS before bilateral auditory cortex tRNS, and the last group was the waiting list. A larger suppression effect was shown for the multisite group (loudness 21.26%, distress 25.90%) when compared with the bifrontal tDCS group (loudness 14.20%, distress 13.03%) and the waiting list group (no effect). The study is limited in the association of tDCS and tRNS, which makes it impossible to analyze the techniques separately [23]. When comparing three different techniques (tDCS, tACS, and tRNS), the tRNS induced the larger transient suppressive effect on tinnitus loudness and distress, and no significant effect was obtained for tDCS and tACS. Thus, results indicate that tRNS may be the most effective single session method for the transient suppression of tinnitus [24].

Acoustic masking is an established method for treatment or alleviation of tinnitus. A competitive acoustic signal is used to modify the perception of tinnitus at a higher cortical level [1]. Acoustic stimulation (AS) in the form of maskers [25], but more elaborated forms for acoustic neuromodulation [26–28], are commonly used. While acoustic neuromodulation and masking requires a relatively long time to induce any effect and is still the subject of critical discussion, residual inhibition (RI) is a well-established principle which can be induced in most tinnitus sufferers after short acoustic stimulation (AS) with white noise (WN) or other sounds. The gradual suppression of tinnitus during a period of RI has been proposed to reflect the resumption of synchronous activity in frequency regions of the auditory cortex [29].

The combination of two or more kinds of treatments, known as bimodal or multimodal stimulation, can be effective for the induction of beneficial neuroplastic effects [9]. A pilot study conducted by Shekhawat et al. in 2015 [30] tested the effects of simultaneous electric and acoustic stimulation.

An improvement in the level of tinnitus perception using tDCS and bilateral broadband noise simultaneously was found in comparison to tDCS or sham alone. Further similar approaches have been published in recent years, namely pilot studies [31, 32], study protocols [30, 33], and a single experimental study [34]. Their results indicate a superior efficacy of electric stimulation combined with acoustic approaches, which highlights the need to conduct large-scale controlled studies to verify these findings.

The approach we propose here, similar to the bimodal approaches above, aims to couple the effects of high-definition tRNS (HD-tRNS) and AS for better temporary tinnitus suppression and a possible reversal of the maladaptive neuroplasticity related to tinnitus. We aim to target the (bilateral) auditory cortex with tRNS, as in former studies [17, 18, 20, 24, 35], and combine it with AS. This specific combination is novel and is based on cortical excitability following tRNS [36] which may lead to more pronounced and sustained effects.

Due to the novelty and complexity of the study and the data to be collected, the absence of any intact local patient or self-help community, and finally the clearly defined outcomes (i.e., tinnitus loudness and distress reductions), public or patient stakeholders could not be involved in the development of the study design.

The number of treatment sessions per condition is in line with well-established general and tinnitus-specific numbers of sessions [18]. Generally, TES can be considered a promising treatment for tinnitus and is practiced in centers around the world, with tDCS being the most widely used method. Research into new protocols and the refinement of established methods is still ongoing, so no specific protocols are recommended as yet [37, 38]. Furthermore, it is important to note that a published guideline for tinnitus treatments reported no evidence for the efficacy of electric stimulation on tinnitus [39].

### Objectives {7}

The proposed project aims to shed more light on the possible effects of simultaneous electrical and acoustic stimulation in tinnitus treatment. Since tRNS has been shown to be the most effective tES method [24], and maskers are a well-established, standard acoustic treatment [25], we want to investigate the potential suppressive effects of these methods combined.

#### Primary objective

The primary objective is to investigate whether simultaneous HD-tRNS and AS improve the levels of subjective tinnitus perception and distress in a clinical population of tinnitus sufferers.

#### Secondary objectives

The changes in neuronal activity patterns after stimulation are to be investigated with regard to the basic mechanisms of tinnitus and treatment effects. Resting state and auditory event-related potential EEG [40] will be recorded for that purpose, as well as to be able to study the putative relationship between brain activation patterns and the subjective tinnitus perception (i.e., tinnitus loudness and tinnitus-related distress) as evaluated by standardized questionnaires and rating scales.

### Trial design {8}

The study is a double-blind, pseudo-randomized (stratified randomization), sham-controlled, crossover within- and between-subject design with two study arms (i.e., testing 2 protocols vs. sham).

Overall, participants will undergo 20 stimulation visits and 6 additional assessment visits (Fig. 1).

**Fig. 1 Fig1:**
[figure not shown]
Flow diagram for crossover of randomized trial. Adapted of CONSORT, 2010

The present protocol follows the Standard Protocol Items Recommendations for Interventional Trials (SPIRIT) guidelines and fulfills the SPIRIT checklist (https://www.equator-network.org/reporting-guidelines/spirit-2013-statement-defining-standard-protocol-itemsfor-clinical-trials/; Accessed 10 June 2021).

## Methods

### Study setting {9}

Single-center study of the University Hospital Zurich (USZ) in cooperation with the University of Zurich (UZH).

The study has been approved by the local ethics committee with registration number BASEC-Nr. 2020-02027. Furthermore, the study is registered in the Swiss Federal Complementary Database (kofam.ch: SNCTP000004051) and in the international trial registry ClinicalTrials.gov (clinicaltrials.gov: NCT04551404).

### Eligibility criteria {10}

#### Inclusion criteria

Participants fulfilling all of the following inclusion criteria may be enrolled in the study:
Male and female participants between 18 and 75 years of agePersistent chronic tinnitus with duration of more than 3 months [41]Signed Informed Consent after being informed about the studyFluent in GermanTinnitus with a Tinnitus Handicap Inventory (THI) Grade 2 to 4 (18–76 points)Willing and being able to attend the study visits

#### Exclusion criteria

The presence of any one of the following exclusion criteria will lead to exclusion of the participant from the study:
Current neurological or psychiatric disordersHyperacusisRegular intake of medication influencing the central nervous system (e.g., neuroleptics, hypnotics, sedatives, and anti-epileptics)Implanted pacemakerSurgical implants in the head region, such as cochlea implantsAsymmetrical hearing (> 20 dB difference between sides), pantonal hearing loss (> 40 dB in any measured frequency up to 2 kHz)Women who are pregnant or breastfeedingIntention to become pregnant during the course of the studyKnown or suspected non-compliance, drug or alcohol abuseParticipation in another study with an investigational drug within the 30 days preceding or during the present studyEnrolment of the investigator, his/her family members, employees and other dependent persons (recommended exclusion criterion by the Swiss Ethics Committee)

#### Dropout criteria

The dropout criteria are participants who discontinue the study without justification.

### Who will take informed consent? {26a}

All participants must agree to contact with the informed consent form before they are submitted to the study procedure. Before the first session, the study personnel explains the aim of the study, the procedures, the duration of sessions, and potential risks and benefits. The participant is also informed that participation is voluntary and that a withdrawal from the study will not affect the treatment or have any other consequences for the participant. Furthermore, withdrawal from the study is possible any time without the obligation to indicate any reason for this decision.

The information is provided in writing and explained verbally by the researcher. The participant should read and understand before dating and signing the document. After approval, a copy of the signed document is given to the participant.

### Additional consent provisions for collection and use of participant data and biological specimens {26b}

This is not applicable.

## Interventions

### Explanation for the choice of comparators {6b}

The study intervention consists of a bilateral HD-tRNS application over temporal regions, parallel to the application of AS in one study arm. Stimulus intensity will be below individual sensation threshold, with a max. of 2 mA. AS will never surpass 85 dB SPL at the ears.

#### Study intervention(s) group A

HD-tRNS bilateral temporal regions combined with AS for 20 minSham HD-tRNS bilateral temporal regions combined with Sham AS for 20 min

#### Study intervention(s) group B = control intervention

HD-tRNS bilateral temporal regions for 20 minSham HD-tRNS bilateral temporal regions for 20 min

Sham conditions are planned for both study arms to test the interventions with respect to placebo effects. The standardized sham HD-tRNS protocol of the DC-Stimulator will ramp up to 2 mA current for 30 s before ramping down to 0 mA to elicit the sensation of a faint tingling on the scalp to imitate the sensation of active tES. The AS sham condition is purposely constructed to present very low sound energy. The tES sham protocol is standard and thus best practice in basic and clinical research whereas the Sham AS is novel in its conception and use (i.e., no specific references available).

### Intervention description {11a}

The study is to be performed in 26 sessions. There are 20 treatment sessions, divided into two blocks, and 6 extra sessions for assessments (Fig. 1, 4).

In order to recruit candidates for the study, those interested in participating are screened by telephone interview. The purpose of this is to assess whether the participant fits the general inclusion/exclusion criteria and to assess their motivation to participate in such a trial. If they are interested in participating in the study, signing the informed consent and the first visit will be performed by one of two dedicated physicians of the Department of Otorhinolaryngology - Head and Neck Surgery at the USZ. Inclusion and exclusion criteria are checked during the second visit. If these are not met, the subject will be excluded from the study. If the participant can be included in the study, their anonymous data is referred to the biometrician for random assignment to study intervention group A or B (Fig. 1).

Treatment period 1 starts with the second session (the first visit of the treatment), which is divided into three stages. In the first stage, the primary and secondary outcome measures are collected on a secure online platform (for more details about the questionnaires, see section “Outcomes {12}” and Fig. 4). In the second stage, the audiological examination and EEG are performed. In the third stage, the first run of treatment is performed. Participants receive the same treatment in sessions 3–10, with intervals of 2–3 days between sessions. After each session, the participant answers a safety questionnaire in order to identify possible side effects of the TES. The 11th session is the final day of treatment in the first block, where the questionnaires of primary outcome measures are applied.

Follow-up 1 starts with session 12, in which the questionnaires of primary outcome measures are repeated in addition to the measurement of minimum masking level (MML), secondary outcome measures (EEG), and questionnaires of other outcomes measures are collected. In session 13, the questionnaires of primary outcome measures are used. This ends the first block of follow-up (Fig. 4).

The second block of the study consists of Treatment Period 2 and Follow-up 2. This block has the same characteristics in the procedure and performance time as the previous sessions (from 2 to 13), the difference is the type of stimulation of HD-tRNS, which contrasts with the one previously carried out (Active/Sham). In session 14, the second period of treatment starts, and the same assessments are made as in session 2. Sessions 15–22 are treatment sessions. In session 23, the same assessments are made as in session 11. Follow-up 2 occurs in sessions 24 and 25, with the same characteristics as follow-up 1 (Fig. 4).

The Close-out is performed in session 26, 7 days after Follow-up 2 and approximately 1 month after Treatment 2 (Fig. 4). In this last session, the primary, secondary, and other outcome measures are performed.

The intervention and evaluation procedures, as well as the explanations regarding the choice of paradigms, can be found in detail below:

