### Strategies to improve adherence to interventions {11c}

Participants will be contacted by phone and email, then appointments will be scheduled in advance according to the availability of each participant. In order to improve adherence, appointments will be available in three shifts, from Monday to Saturday.

The questionnaires will be collected on an easy-to-navigate online platform before each session at which the participants are present and in an online form in sessions 13 and 25. Additionally, after each therapy session, a safety questionnaire will be applied in order to identify any side effects resulting from the stimulation.

In case of non-compliance, such as absence in sessions, the participants will be contacted via telephone or email, and asked about continuation or early termination of the study.

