### Adverse event reporting and harms {22}

Neuromodulation is a safe procedure, causing no apparent short- or long-term harm.

Only low adverse events are possible, such as headaches, burning, itching, tingling, tiredness, heat, redness, irritation, difficulty concentrating, and pain. However, the side effects will be monitored after each session through a safety questionnaire. In cases of the appearance of secondary effects to the treatment, the investigators are requested to report any untoward clinical event on the adverse event page of the case report form (CRF). All details will be reported, including the time of occurrence, symptoms and signs, severity, duration, and causal relationship with the treatment.

In case of discomfort to adverse events, the case will be analyzed by the health professionals involved, who will decide whether changes in the treatment could benefit the participants and reduce the side effects or whether participation in the study should be terminated.

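### The only scheduled safety questionnaire follows therapy sessions and its scope differs between sections, so effects that start later or persist at follow-up rest on spontaneous reporting

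*Protocol article*

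**What the plan says.** Three sections of the protocol article describe the safety questionnaire.

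- Intervention description {11a}: "After each session, the participant answers a safety questionnaire in order to identify possible side effects of the TES".
- Strategies to improve adherence {11c}: "after each therapy session, a safety questionnaire will be applied in order to identify any side effects resulting from the stimulation".
- Adverse event reporting and harms {22}: "the side effects will be monitored after each session through a safety questionnaire".

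Section {22} adds a reporting route for effects that come to light: "the investigators are requested to report any untoward clinical event on the adverse event page of the case report form (CRF"). It then says "All details will be reported, including the time of occurrence, symptoms and signs, severity, duration, and causal relationship with the treatment". The effects it expects are these: "Only low adverse events are possible, such as headaches, burning, itching, tingling, tiredness, heat, redness, irritation, difficulty concentrating, and pain". Section {11b} gives a similar list with nausea added, and says in general terms that participants are watched for symptoms, without a method or a time window.

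Under Acoustic stimulation (AS), group A's active condition is white noise at MML + 10 dB for 20 minutes, capped at 85 dB SPL.

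**The concern.** The combination of HD-tRNS with sound is the trial's novel element, and {22} already takes the position that neuromodulation causes no apparent harm in the short or long term. A trial that will be cited on safety needs a scheduled question that could contradict that position.

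As written, the scheduled question is attached to the therapy session. Several effects that the article itself names, such as headache, tiredness and difficulty concentrating, can begin after the participant has gone home. Worsening that shows itself at follow-up or close-out also falls outside the schedule. For sound, {11a} points the questionnaire at the electrical part, and no list mentions louder or changed tinnitus, muffled hearing or sound intolerance. At stake is whether the harms of active against sham, and of bimodal against electrical stimulation alone, are ascertained in the same way for every participant or depend on who chooses to speak up.

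**Working it through.** No sample-size or power figure bears on this point. The check is a count of sessions and a comparison of sections.

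**1. Sessions covered.** From {11a}, treatment sessions are 2–11 and 14–23, so 10 + 10 = 20. The other sessions are 1, 12, 13, 24, 25 and 26, which makes 6. The total is 20 + 6 = 26, as the article states. On the wording of {11c} (each therapy session), the questionnaire is given at 20 of 26 sessions. Session 1 precedes any stimulation, so five assessment sessions remain at which a treatment-related effect could be present. The text names the questionnaire at 0 of these 5, although {11a} does set out what is collected there.

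**2. Scope.** Set side by side:

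- {11a}: side effects of the TES, that is, the electrical component.
- {11c}: side effects of the stimulation, with no component singled out.
- {22}: side effects after each session, plus any untoward clinical event on the CRF.

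The first is narrower than the other two. Anyone building the form from {11a} could leave out sound, and anyone building it from {11c} would not.

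**3. Expected effects.** Every effect listed in {11b} and {22} is of a kind associated with electrical stimulation. Group A's active block also delivers 10 sessions × 20 minutes = 200 minutes of white noise. The residual inhibition scale allows a rating of much louder, so the article recognises that tinnitus can rise after sound.

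**4. Look-back.** Section {11c} separates two streams: the online questionnaires are completed before each attended session (and remotely at 13 and 25), while the safety questionnaire comes after therapy. No question about the interval since the last visit is described in either stream. The CRF clause in {22} begins to operate once an effect has appeared. It records onset and duration but schedules no enquiry.

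**5. Efficacy measures as a substitute.** From {11a}, VAS loudness and distress are repeated at sessions 11, 12, 13, 14, 23, 24, 25 and 26, and MML at least at 12, 24 and 26. These go into the primary analysis of change, where a few participants who worsen can be offset by others who improve. Two inconsistencies weaken the substitute further. Other outcome of interest says that audiometry and the hyperacusis questionnaire are taken only at the second visit, whereas {11a} and {13} have the other outcomes repeated. And {11b} leaves dropouts out of the analysis while {20c} states intention to treat. If {11b} governs, a participant who leaves because of worsening also disappears from VAS and MML.

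**The case against.** The strongest reply is that the article already has more than the questionnaire. Any untoward event can go on the CRF with its time of occurrence, participants return every 2–3 days during treatment, urgent treatments are recorded ({11d}), loudness is rated repeatedly, sound is capped at 85 dB SPL, and hyperacusis is an exclusion criterion. Safety data are to be listed and summarised ({20a}). Fig. 4 and the full ethics protocol are not shown and may contain the items and the reporting window. All of this stands, and it limits the point. It does not supply a scheduled look-back question or settle the scope of the questionnaire.

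Several stronger readings are tempting, and the documents do not support them.

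- A reader might infer that acoustic harms have no coverage at all. Sections {11c} and {22} are not restricted to the electrical part, and the list in {22} is given as examples.
- A reader might link the timing to the statement in {6a} that tRNS can "reliably increase the cortical excitability up to 1 h after a stimulation of 10 min". That concerns a physiological after-effect, not a side effect, and nothing says that harms follow the same window.
- A reader might take the questionnaire as given at the moment stimulation stops, and count the 9 intervals × 2–3 days = 18–27 days per block as unobserved. The text says only that it follows the session. That count assumes that participants report nothing from earlier days, which is not stated.
- A reader might conclude that the harm comparison is biased toward no difference, because sham is designed "to elicit the sensation of a faint tingling on the scalp to imitate the sensation of active tES". That depends on questionnaire items that are not shown.

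**Conclusion.** The point holds in a limited form. The one scheduled harms instrument is tied to therapy sessions (20 of 26, and none of the five assessments after treatment), its stated scope differs between {11a} and {11c}/{22}, and no auditory effect is named for a treatment that includes sound. Later-onset effects, and effects present at sessions 12, 13, 24, 25 or 26, therefore rest on spontaneous reporting. Auditory worsening is otherwise visible only through efficacy outcomes.

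The number of events that would be missed cannot be estimated from the document. The conclusion assumes that the schedule figure and the full protocol add no safety enquiry at follow-up. If they do, only the scope of the questionnaire and the absence of auditory effects from the article's lists remain to be settled. The primary efficacy analysis is not affected. The change is worth making because it is inexpensive and the combined treatment is new.

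**What to change.** 1. Reconcile {11a}, {11c} and {22} so that all three state that the safety questionnaire covers both tRNS and AS.
2. Add a short safety question about the time since the last visit to the online set already completed before each session, and include it at sessions 12, 13, 24, 25 and 26, unless Fig. 4 or the full protocol already does so. Keep the existing post-session questionnaire.
3. Include items on louder or changed tinnitus, muffled hearing and sound intolerance, asked identically in both arms and both blocks so that blinding and comparability are kept.
4. Tabulate responses by active or sham block within each arm. Answers given before the first treatment of block 2 (session 14) refer to the period after block 1 and should be counted there.

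The cost is a few minutes per visit on a platform already in use, and somewhat more reported events, many of them probably minor. No treatment, dose or visit changes.
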